## Abstract

**Background:**

Breast-conserving surgery (BCS) and whole breast radiation therapy (WBRT) are the standard of care for early-stage breast cancer (BC). Based on the observation that most local recurrences occurred near the tumor bed, accelerated partial breast irradiation (APBI), consisting of a higher dose per fraction to the tumor bed over a reduced treatment time, has been gaining ground as an attractive alternative in selected patients with low-risk BC. Although more widely delivered in postoperative setting, preoperative APBI has also been investigated in a limited, though increasing, and number of studies. The aim of this study is to test the feasibility, safety and efficacy of preoperative radiotherapy (RT) in a single fraction for selected BC patients.

**Methods:**

This is a phase I/II, single-arm and open-label single-center clinical trial using CyberKnife. The clinical investigation is supported by a preplanning section which addresses technical and dosimetric issues. The primary endpoint for the phase I study, covering the 1st and 2nd year of the research project, is the identification of the maximum tolerated dose (MTD) which meets a specific target toxicity level (no grade 3–4 toxicity). The primary endpoint for the phase II study (3rd to 5th year) is the evaluation of treatment efficacy measured in terms of pathological complete response rate.

**Discussion:**

The study will investigate the response of BC to the preoperative APBI from different perspectives. While preoperative APBI represents a form of anticipated boost, followed by WBRT, different are the implications for the scientific community. The study may help to identify good responders for whom surgery could be omitted. It is especially appealing for patients unfit for surgery due to advanced age or severe co-morbidities, in addition to or instead of systemic therapies, to ensure long-term local control. Moreover, patients with oligometastatic disease synchronous with primary BC may benefit from APBI on the intact tumor in terms of tumor progression free survival. The study of response to RT can provide useful information about BC radiobiology, immunologic reactions, genomic expression, and radiomics features, to be tested on a larger scale.

**Trial registration:**

The study was prospectively registered at clinicaltrials.gov (NCT04679454).

## Background

Whole breast radiation therapy (WBRT) after breast-conserving surgery (BCS) is the standard of care for patients with early-stage breast cancer (BC) [1]. Over the last two decades, radiotherapy (RT) for BC has undergone major changes in fractionation, techniques and target volumes [2–4].

Hypofractionation is now considered the preferred schedule for adjuvant WBRT on the basis of the results of dedicated randomized phase III studies showing equivalent tumor control, improved acute toxicity and similar late toxicity rates compared to conventional fractionation [5–7]. Hypofractionation has been successfully applied in the setting of accelerated partial breast irradiation (APBI) where the treatment is given only to the tumor bed as the region at higher risk of relapse [8–10]. A number of APBI phase III trials using different techniques have showed that, in selected patients, APBI achieved a satisfactory local control, comparable with that of WBRT, but with fewer side effects, greater convenience, better quality of life, reduced costs [11–15]. The safety and the efficacy of APBI delivered in postoperative setting have stimulated investigations in the preoperative field as well. In this context, preoperative APBI can be regarded as anticipated boost, followed by WBRT after surgery, or can be used with neoadjuvant purpose, to reduce the size of the lesion allowing more conservative surgery and to test the tumor sensibility. The latter investigation might open to the possibility of a definitive RT with curative intent. Older and/or frail women that are less likely to receive standard of care treatments, often because of medical comorbidities, might benefit the most [16–18].

The algorithm to replace surgery with RT has proved to be successful in the treatment of oligometastases. Short courses of high dose stereotactic ablative radiosurgery (SRS) have frequently being used as alternatives to surgery for oligometastases. Starting from the benefits observed for solitary brain metastases, the use of SRS has been expanded to include extracranial sites. Scorsetti and coll. [19], considering a cohort of 33 BC oligometastatic patients, observed local control rates of 98 and 90% at 1 and 3 years, with complete and partial response rates of 53 and 34% respectively. These results may provide the rationale to investigate the effect of delivering high-dose single fraction to small primary BC.

The feasibility and the efficacy of a pre-operative radioablation approach on primary BC have been investigated in few clinical studies, using different technique, dose/fraction, number of fractions, total dose and irradiated volumes. Preliminary reports demonstrate low toxicity and a rate of pathological response worthwhile exploring further [20–27].

The aim of the present study is to test the feasibility, safety and efficacy of preoperative RT in a single fraction for selected BC patients.

## Methods/design

### Aim, design, and setting of the study

This is a monocentric phase I/II, single-arm and open-label trial planning to enroll a maximum of 79 patients over 5 years and using CyberKnife to deliver the ablative dose (18–24 Gy) to the tumor before surgery. The clinical investigation includes a preplanning section in which technical issues (contouring, set-up, dosimetry, treatment delivery, etc.) are addressed. The project was registered at clinicaltrials.gov (NCT04679454) and was approved by institutional Ethical Committee (identification number 1308).

### Study population

#### Participant characteristics and eligibility criteria

Inclusion and exclusion criteria are summarized in Table 1.

**Table 1 Tab1:** Inclusion and exclusion criteria

ELIGIBILITY CRITERIA	
**INCLUSION CRITERIA**	Histologically proven unifocal adenocarcinoma of breast cancer
	cT1-cT2 cN0
	Age ≥ 18 years old
	Good general condition (ECOG 0–2)
	Planned surgery (BCS or mastectomy)
	Written informed consent
**EXCLUSION CRITERIA**	Tumor too close to skin or chest wall
	Pure non-invasive tumor
	Prior RT to the chest
	Neoadjuvant chemotherapy
	Coagulation, connective, autoimmunitary disorders
	Previous malignancies

*List of abbreviations*: *BCS* breast conserving surgery, *ECOG* Eastern Cooperative Oncology Group, *RT* radiotherapy

After study enrollment, a core biopsy is performed for tumor characterization. At the time of core biopsy, at least 3 gold fiducial markers, of 1 mm × 1.5 mm size and compatible with any radiologic examinations, are placed around the tumor under ultrasound guidance for RT target localization along the 3 axes.

Radiological work-up is completed with preoperative magnetic resonance imaging (MRI) in supine and prone position.

### Study design

The research project comprises 6 tasks:Technological assessment – a pre-clinical investigation of radioablation feasibility using CyberKnife is conducted to establish protocol procedures;Patients enrollment and monitoring - patients are enrolled according to the inclusion criteria. Maximum acute toxicity at 1 and 2 weeks after radioablation is evaluated to modulate the accrual throughout the phase I dose escalation study;Histopathologic analysis - tumor characteristics and radiation response are investigated through histopathologic analyses of biopsy and surgical specimen;Radiology and Radiomics tasks - imaging features extracted from pre- and post- radioablation MRI are quantitatively and semi-quantitatively analyzed to identify imaging markers of radiation response;Molecular pathology – expression of genes involved in tumor–immune system interactions is analyzed through next generation sequencing (NGS) assays.

#### Phase I study

Dose escalation is designed as a traditional 3 + 3 rule-based study. This study design is the prevailing method for conducting phase I cancer clinical trials since it avoids the selection of phase II doses that cause a treatment-limiting toxicity in more than 17% of subjects [28]. This rule-based design proceeds with cohorts of three patients testing three dose levels: 18 Gy, 21 Gy and 24 Gy. Starting from the lowest prescription dose, if none of the three patients in the first cohort experiences a dose limiting toxicity (DLT), other three patients will be treated at the next dose level. However, if one of the first three patients experiences a DLT, three more patients will be treated at the same dose level. The dose escalation continues up to the 24 Gy dose level until at least 2 patients among a cohort of 3 to 6 patients experience DLT. The recommended dose for subsequent phase II trial is defined as the dose level just below this toxic value. Maximum tolerated dose (MTD) is decided when 6 patients are treated at a dose level and a maximum of 1 out 6 (17%) patients experiences DLT. The starting dose level of 18 Gy is considered to be safe based on the basis of previous studies [22]. Phase I study will enroll a maximum of 18 patients, depending on the number of dose level escalations and the number of DLTs observed.

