### Endpoints of the study

#### Phase I endpoints

Primary endpoint of the phase I study is to identify MTD, which is the dose that meets a specific target toxicity level (no grade (G) 3–4 toxicity).

Outcome measures is obtained through acute skin/soft tissue toxicity, measured according to NCI CTCAE v. 4.03 [34]. Any G3–4 toxicity related to radioablation is considered dose limiting (DLT).

Secondary endpoints include chronic toxicity, cosmesis, post-surgery complications, outcomes of survival and relapse, extra-cutaneous complications and pCR.

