#### Phase II endpoints

Primary endpoint is the evaluation of the efficacy measured in terms of pCR rate.

Outcome measures is obtained through the pCR rate after surgery, according to the Modified Residual Cancer Burden (RCB) index.

Secondary endpoints include acute/chronic toxicity, cosmesis, post-surgery complications, outcomes of survival and relapse, extra-cutaneous complications.

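### The 17% in the 3+3 design is the highest observed DLT proportion accepted, not a limit on the true rate at the phase II dose, and the MTD has two conflicting toxicity targets

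*Protocol article*

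**What the plan says.** The Phase I study section of the protocol article states: "Dose escalation is designed as a traditional 3 + 3 rule-based study". It gives as the reason for this choice that "it avoids the selection of phase II doses that cause a treatment-limiting toxicity in more than 17% of subjects", citing a reference. The design runs in "cohorts of three patients testing three dose levels: 18 Gy, 21 Gy and 24 Gy".

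The rules in that section are:
- With no DLT in three patients, the next level is opened.
- With one, "if one of the first three patients experiences a DLT, three more patients will be treated at the same dose level".
- Two or more DLTs among three to six patients mark a level as toxic, and the level below is recommended for phase II.
- The MTD is settled when six patients have been treated at a level and at most one of them, given as 17%, has a DLT.

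The toxicity target is stated elsewhere in different terms. The Methods part of the Abstract speaks of an MTD "which meets a specific target toxicity level (no grade 3–4 toxicity"). The Phase I endpoints section defines the MTD as the dose "which is the dose that meets a specific target toxicity level (no grade (G) 3–4 toxicity"). That section also counts every grade 3–4 toxicity related to radioablation as a DLT.

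The dose chosen is then given in phase II, planned for 61 patients. There, toxicity is a secondary endpoint: "Secondary endpoints include acute/chronic toxicity, cosmesis, post-surgery complications".

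**The concern.** There are two separate faults.

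First, the 17% sentence describes what the selected dose causes in subjects, so it reads as a limit on the dose's true toxicity. The only source of 17% in the section is the observed cut-off of one in six. A count from three to six patients cannot bound a true rate at that level. A reader who takes the sentence at face value will believe the phase II dose has been screened far more tightly than it has.

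Second, a target of no grade 3–4 toxicity and a tolerance of one DLT in six cannot both define the MTD when every related grade 3–4 event is a DLT. This concerns the definition of the phase I primary endpoint. A level with one DLT in six patients is acceptable under one section and misses the target stated in two others.

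**Working it through.** **The article's own figures.** 1/6 = 16.7%, rounded to 17%. Three levels × six patients = 18, the stated phase I maximum. Both are correct, so the fault lies in what the 17% is said to mean.

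**Precision of one in six.** The exact (Clopper-Pearson) 95% interval for 1/6 is 0.4% to 64%.

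**Chance that a single level passes.** Let p be its true DLT rate. The article gives no value of p, so a range is shown.

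- Escalation rule (0/3, or 1/3 then 0/3): (1−p)³ + 3p(1−p)² × (1−p)³.
- Six-patient MTD rule (at most 1/6): (1−p)⁶ + 6p(1−p)⁵.

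At p = 0.30, the escalation rule gives 0.343 + 0.441 × 0.343 = 0.494. The six-patient rule gives 0.118 + 0.303 = 0.420 (from unrounded terms).

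| True DLT rate | Escalation rule | Six-patient MTD rule |
|---|---|---|
| 17% | 77% | 73% |
| 20% | 71% | 66% |
| 25% | 60% | 53% |
| 30% | 49% | 42% |
| 40% | 31% | 23% |

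**Chance that the whole trial carries forward a dose with a true rate above 17%.** This needs assumed rates at 18, 21 and 24 Gy. The dose carried forward is the level below the first toxic one, or 24 Gy if none is toxic, without requiring six patients at it.

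- 10/20/30%: the levels pass with probability 0.906, 0.709 and 0.494. Selecting 21 Gy: 0.906 × 0.709 × (1 − 0.494) = 0.325. Selecting 24 Gy: 0.906 × 0.709 × 0.494 = 0.317. Together 0.64.
- 5/10/30%: only 24 Gy exceeds 17%. 0.973 × 0.906 × 0.494 = 0.44.
- 2/5/10%: no level exceeds 17%, so 0.

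If the chosen level must also be filled to six patients with at most one DLT, stepping down when it fails, the first two become 0.61 and 0.37.

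**The two targets side by side.**

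| Section | What qualifies a dose |
|---|---|
| Abstract, Methods | No grade 3–4 toxicity |
| Phase I endpoints | No grade 3–4 toxicity; any related grade 3–4 event is a DLT |
| Phase I study | At most one DLT in six |

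The sections disagree whenever a level passes with exactly one DLT, which is not a rare outcome. At p = 0.20 under the escalation rule, that path has probability 0.384 × 0.512 = 0.197 out of 0.709, or 28% of passes.

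**The case against.** The sentence on 17% is background, attributed to a reference that is not at hand, and the same section later ties 17% to an observed count. Read that way it is loosely worded rather than false, and removing it would change no cohort, rule, endpoint or sample size. This stands as far as it goes. But as a statement about observed counts the sentence only repeats the rule, and the article offers it as the reason for choosing the design.

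The zero target can likewise be read as naming the grade of toxicity that counts, since the DLT definition follows shortly after it. That reading is possible, but the words describe a target level, and the Abstract repeats them without the DLT definition.

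Several stronger readings are tempting, and the document does not support them.

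- **That the trial will pick a too-toxic dose in about half or two-thirds of cases.** The 49% is the chance that one level with a true 30% rate passes the escalation rule once it has been reached; the six-patient rule gives 42%. The 64% belongs to one assumed set of rates. The Discussion reports no DLT up to 21 Gy in an earlier single-fraction series with 16 patients at 21 Gy. At a true 20% rate, 0/16 has probability 0.8¹⁶ = 2.8%. That series used IMRT and a different population, so this is only indicative, but it argues against treating 10/20/30% as the expected case.
- **That the 17% claim is what justifies treating 61 more patients.** The 61 comes from the response hypotheses of 9% and 20% in the Phase II study section.
- **That phase II needs a formal toxicity pass mark at 17%.** Requiring an exact one-sided 95% upper limit below 17% would allow at most 5 DLTs in 61, or 6 in 67 with six phase I patients pooled. A dose with a true 10% rate would meet this only 42% or 49% of the time. Pooling would also reuse patients on whom the dose was selected, which biases the estimate downward.

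**Conclusion.** Both parts hold and should be corrected. The 17% is the highest observed DLT proportion accepted, and the design does not keep doses with a higher true rate out of phase II. A level with a true rate of 20% to 40% passes with probability 71% down to 31% under the escalation rule, and 66% down to 23% under the six-patient rule, so the conclusion does not depend on which rule is applied. These figures assume independent patients with a common DLT rate at each level.

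The trial-level risk cannot be fixed from the document. It ranges from 0% to 64% over the three scenarios shown, according to the assumed rates.

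The conflict between a target of no grade 3–4 toxicity and acceptance of one DLT in six is plain from the text. A reader might infer that phase I will be declared met or failed according to the section consulted. That goes too far, because the stated endpoint is to identify the MTD and the Phase I study section holds the only operating rule. What is established is that the MTD has two definitions that disagree.

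**What to change.** - In the Phase I study section, replace the 17% assurance with a statement that 17% (1/6) is the maximum observed DLT proportion accepted at the MTD.
- Add the pass probabilities over a range of true DLT rates, for both the escalation rule and the six-patient MTD rule.
- Reconcile the Abstract, the Phase I study section and the Phase I endpoints section to one toxicity target. Which target applies is for the investigators to decide; this review does not propose one.
- Report the phase II DLT rate with an exact confidence interval, as description only and without a pass criterion.

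The cost is wording, a short table and one interval, with no extra patients and no change to the escalation scheme. The drawback is that the safety property claimed for the design becomes less favourable.

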#### Phase II study

The recommended dose level found in the first phase will be delivered in the phase II study. The primary endpoint of the phase II study is the rate of pathological complete response (pCR). In the current research project, radioablation is expected to be as effective as a single drug agent. A pCR rate of 20% is chosen to test the efficacy of radioablation.

A study requires 61 patients to decide whether the proportion of responders, i.e. P, is ≤9% or ≥ 20%. If the number of responses is 10 or more, the hypothesis that *P* ≤ 9% is rejected with a target error rate of 5%. If the number of responses is 9 or less, the hypothesis that *P* ≥ 20% is rejected. Therefore, in the projected population of 61 patients, at least 10 patients with pCR are required to reject the null hypothesis of no treatment efficacy.

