### Treatment

Radioablation is performed within 4 weeks since patient entering the study and no systemic therapy is allowed in the pre-operative settings.

Surgical tumor removal is scheduled within 8 weeks from radioablation.

All patients receive postoperative RT without boost to the tumor bed, preferably with hypofractionation (preferably, 2.67 Gy × 15 fractions). Systemic therapy is administrated according to the institutional guidelines.

Post-surgical complications as well as radiation side effects are collected and follow-up is scheduled on regular basis throughout 3 years.

An overview of the treatment workflow is reported in Fig. 1.

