
As observed for postoperative APBI, different techniques have been used to perform preoperative APBI: three-dimensional conformal RT (3D-CRT), intensity modulated RT (IMRT), volumetric-modulated arc-therapy (VMAT), SRS and stereotactic body RT (SBRT), brachytherapy (BRT) and proton beam therapy (PBT) [39–43]. Main preoperative APBI studies published in the literature are summarized in Table 2, while Table 3 and Table 4 describe the ongoing clinical trials. Because of the complexity of BRT and the requirement of a larger PTV for 3DCRT/IMRT, stereotactic techniques are preferred for preoperative approach to BC, given their proven efficacy and safety in the treatment of a great variety of primary and metastatic tumors [44–47]. In the current study, single fraction preoperative radioablation is investigated using robotic SBRT with CyberKnife system, which allows smaller margins, less radiation exposure to adjacent normal tissue and, potentially, better cosmetic outcomes. Moreover, Cyberknife is capable of tracking the target volume during irradiation to achieve high conformity and dose gradient to the tumor. The current research project plan focuses first on the identification of the maximum tolerated dose, whose efficacy is investigated in terms of pCR rate in the phase II study. The starting dose is 18 Gy in single fraction, which can be considered relatively safe. This dose level was also used by Horton et al. [22] in their phase I dose escalation trial of single-dose preoperative RT for early stage unifocal BC patients. Dose escalation levels were 15 Gy (*n* = 8), 18 Gy (n = 8) or 21 Gy (*n* = 16), delivered with IMRT. Post-operative conventional RT was administered to patients not satisfying the eligibility criteria following surgical resection (*n* = 3). No dose-limiting toxicity was observed up to 21 Gy and, at a median follow-up of 23 months, no evidence of tumor progression was documented. Physician-rated cosmetic outcomes were good/excellent and chronic toxicities were low in patients receiving preoperative RT only. Among the 3 patients receiving post-operative RT, one with a connective tissue disorder developed two grade 3 chronic toxicities, and one with diabetes suffered from wound infection, while all of them presented a fair/poor cosmetic outcome. Another phase I dose-finding SBRT trial was conducted by Bondiau et al. [21], where 5 dose levels (from 19.5 Gy to 31.5 Gy in 3 fractions) were tested, using a robotic SBRT system during the course of preoperative chemotherapy in locally advanced BC patients. Surgery and conventional post-operative RT were performed 6–8 weeks after neoadjuvant chemoradiotherapy. After observing only one grade 3 toxicity (dermatologic in nature) at 28.5 Gy, the authors concluded that the lower dose of 25.5 Gy in 3 fractions could be used for the phase 2 trial. The French series showed high rate of pCR (36%) and breast-conserving surgery (92%). These excellent results were likely due to the synergic and additive effect of concomitant radiochemotherapy. Relying on RT alone, the rate of pCR is expected to be lower, ranging from 10 to 15%. In the abovementioned series, all patients received WBRT without boost to the tumor bed and none of them presented any excess of toxicity, despite the fact that preoperative APBI was delivered concomitantly with neoadjuvant chemotherapy. This favorable outcome is in contrast to the fair/poor cosmesis of the patients enrolled by Horton and coll., who received both pre- and post-operative RT [22]. Horton and coll. Explained such an inconsistency between the 2 series with the presence of comorbidities, affecting the tolerability to the treatment, and with differences in fractionation schedules.

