
**Table 2 Tab2:** Summary of the studies on preoperative breast cancer radiotherapy

Author and year	Inclusion criteria	n of pts	Treatment	Systemic therapy	Time to surgery	Postoperative RT	Outcomes	Toxicity	Follow-up (months)
Bondiau et al., 2013 [21]	Unifocal BC not suitable for BCS, HER2 negative	26	Robotic SBRT (Cyberknife)/19,5–31.5 Gy/3 fr (5 dose levels)	CHT	4–8 weeks after last CHT	Yes, 3D-CRT	pCR 36% (NS) 92% BCS rate 96% ORR	none	30
Horton et al., 2015 [22]	Age > 55 years, T1 BC or low- intermediate DCIS ≤2 cm, cN0, ER + and/or PR+, HER2-	32	IMRT/15–21 Gy (3 dose levels)/1 fr	none	within 10 days after RT	Yes (Only to patients not satisfying eligibility criteria after BCS)	Significant increase in MRI post- radiation vascular permeability and decreased cellular density	13 Grade2; 2 Grade 3	23
van der Leij et al., 2015 [23]	Age > 60 years, invasive, unifocal BC ≤ 3 cm on MRI, non-lobular, negative SNB	70	3D-CRT or IMRT or VMAT/40 Gy/10 fr	none	6 weeks after RT	No	2 local recurrences	11% mild-moderate 23 induration at 12 months; 2% mild-moderate fibrosis at 24 months	23
Nichols et al., 2017 [24]	Unifocal invasive BC < 3 cm at mammography or MRI, cN0	27	3D-CRT /38.5 Gy/10 fr (twice daily)	none	> 21 days after RT	No	pCR 15% (NS) ORR 88.9%; Ki-67 reduction after RT in 70.4%	PRCO fair and poor in 17 and 5% at 1 year, respectively	43
Tiberi et al., 2020 [27]	postmenopausal status, age > 65 years, stage I (cT1N0) invasive BC, unifocal luminal A, ER+, her2-negative, G1–2	10	SBRT 20 Gy/1fr	none	11–13 weeks after RT	Yes if: Grade 3, lymphovascular invasion, pT4, triple neg, extensive DCIS, tumor size > 3 cm, lobular histology	pCR: 0 (median residual cellularity was 3% in 8 patients; for the other 2 patients no response at all was observed)	none	< 12
DOSIMETRIC STUDIES									
Charaghvandi et al., 2015	Tumor size up to 30 mm, scheduled for BCS and WBI	20	IMB and VMAT 15 Gy/1 fr + integrated ablative boost of 20 Gy	none	–	–	Dosimetrically feasible with IMB and VMAT	–	–
Yoo et al., 2015 [44]	Patients enrolled on a preoperative, dose escalation, single fraction PBI clinical protocol	16 (8 + 8)	3D-CRT, non-coplanar IMRT, coplanar IMRT, VMAT 15 Gy/1fr and 18 Gy/1 fr	none	–	–	IMRT plans provided homogeneous and conformal target coverage, skin sparing, and short delivery time	–	–

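### Phase II is sized on a 20% pCR rate while the Discussion expects 10–15% for radiotherapy alone; the two are not reconciled, and the 10-of-61 rule rarely succeeds in the lower range

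*Protocol article*

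**What the plan says.** Protocol article, Phase II study: the pCR rate is the primary endpoint. Radioablation is expected to match a single drug agent, for which no rate is given, and then "A pCR rate of 20% is chosen to test the efficacy of radioablation". The sizing follows: "A study requires 61 patients to decide whether the proportion of responders" is at most 9% or at least 20%. With 10 or more responses the 9% hypothesis "is rejected with a target error rate of 5" per cent. With 9 or fewer, the hypothesis of at least 20% is rejected. The section sums up: "in the projected population of 61 patients, at least 10 patients with pCR are required to reject the null hypothesis of no treatment efficacy". Power is not stated.

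Protocol article, Discussion: after attributing a 36% pCR rate to concomitant radiochemotherapy in a three-fraction series, the text says: "Relying on RT alone, the rate of pCR is expected to be lower, ranging from 10 to 15" per cent.

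Protocol article, Treatment: "no systemic therapy is allowed in the pre-operative settings".

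Protocol article, Table 2: two radiotherapy-alone studies report a pCR rate. One (38.5 Gy in 10 fractions, 27 patients) gives 15%. The other (20 Gy in one fraction, 10 patients) gives "pCR: 0 (median residual cellularity was 3% in 8 patients; for the other 2 patients no response at all was observed".

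**The concern.** The article gives two expectations for what looks like the same quantity. The Methods expect an efficacy that is put at 20%; the Discussion expects 10–15% for radiotherapy without drugs, which is what patients here receive before surgery. The lower range lies wholly between the null rate (9%) and the alternative (20%), and its bottom end is one percentage point above the null.

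At stake is how the go/no-go result will be read. The success threshold is an observed rate of 10/61 = 16.4%, above the top of the Discussion's range. If the Discussion is right, the likeliest outcome is a failed test, and the wording of the Phase II study section, which ties the test to a null of no treatment efficacy, invites readers to take that as evidence that the treatment does not work.

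**Working it through.** **Inputs.** n = 61, cutoff r = 10, p0 = 9%, p1 = 20%, error rate 5% (Phase II study). The test is one-sided by construction, since success requires enough responses. Expected rate for radiotherapy alone: 10–15% (Discussion). Power is not stated; 80% is inferred below.

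**Step 1: reproduce the design.** With X ~ Binomial(n, p), find the smallest n for which some r gives P(X ≥ r | 0.09) ≤ 0.05 and P(X ≥ r | 0.20) ≥ 0.80. The search returns n = 61, r = 10:

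- alpha = P(X ≥ 10 | 61, 0.09) = 0.0449
- power = P(X ≥ 10 | 61, 0.20) = 0.8041

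The plan's figures reproduce exactly. A normal approximation gives about 54 (one-sided, 80%) or 67 (two-sided, 80%), so the exact design was evidently used.

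**Step 2: the same rule at the Discussion's rates.** P(success) = P(X ≥ 10 | 61, p):

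| True pCR | P(10 or more) | P(9 or fewer) |
|---|---|---|
| 9% | 4.5% | 95.5% |
| 10% | 8.0% | 92.0% |
| 12.5% | 22.7% | 77.3% |
| 15% | 43.4% | 56.6% |
| 20% | 80.4% | 19.6% |

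Over 10–15% the chance of success is 8–43%, and the chance of 9 or fewer responses is 57–92%.

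**Step 3: what failing results look like.** 7/61 = 11.5%, 8/61 = 13.1%, 9/61 = 14.8%. All three fail the rule, and all three lie inside the range the Discussion expects.

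**Step 4: do the article's own data settle the rate?** 15% of 27 is about 4 patients (inferred from the percentage). Adding 0 of 10 gives 4/37 = 10.8%, with an exact 95% interval of 3.0–25.4%. For 0/10 alone the upper limit is 30.8%. Both intervals contain 20%.

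**The case against.** The strongest reply is that a design rate is not a forecast. In a single-arm phase II trial the upper rate may be the one that would make the treatment worth pursuing. The article's stated ambition, finding patients in whom surgery could be omitted, makes a demanding bar reasonable. On that reading a low chance of success at 10–15% is intended, and every two-hypothesis design has a zone between its rates where it decides poorly. This reading is available, but the Phase II study section does not adopt it: 20% follows directly on an expectation of efficacy and is never called a minimum worthwhile rate.

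It is also fair that the 10–15% sentence is an unreferenced Discussion remark. It was made to explain a chemoradiation series and does not name this trial's single-fraction 18–24 Gy regimen. It remains the only numerical expectation for radiotherapy alone in the article.

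A reader might go further and infer that 20% is refuted by the article's own evidence, or that the trial is mis-sized. The documents support neither. The two Table 2 studies differ from each other in fractionation and from this trial in population: the single-fraction study took luminal A, grade 1–2 patients over 65, whereas Table 1 here sets no subtype limit and admits ages 18 and over. Pooling them is weak evidence, and the interval reaches 25.4%. The sample size is right for the rates it names.

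**Conclusion.** The concern holds as an inconsistency with a measurable consequence. The 61-patient, 10-response rule is correct for 9% against 20% (alpha 4.5%, power 80.4%). The 20% rests only on an unquantified analogy, and the article elsewhere expects 10–15% from the kind of treatment given here, where the rule succeeds with probability 8.0% to 43.4%. As written, a reader cannot tell whether 20% is expected or merely required, and a result the Discussion would call expected could be reported as no efficacy.

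This rests on three assumptions: that the Discussion's general statement about radiotherapy alone applies to this regimen; that all 61 patients are evaluable; and that the inferred 80% power target is what the design intended. The first is the most open to dispute, since a regimen of up to 24 Gy could do better, although the article does not argue this.

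**What to change.** Keep 61 patients and the cutoff of 10, and make three changes of wording.

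1. Reconcile the Phase II study section with the Discussion. Either support 20% as the expected rate with radiotherapy evidence, or declare it a minimum rate of interest and say that it is not an expectation.
2. State the power of the rule at true rates of 10%, 12.5%, 15% and 20%: 8.0%, 22.7%, 43.4% and 80.4%.
3. State that 9 or fewer responses means that a rate of 9% or less was not rejected and the 20% target was not met. It does not show absence of efficacy, since 7 to 9 responses (11–15%) lie inside the article's own expected range.

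The cost is text only, plus a less favourable stated power.

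A different hypothesis pair is not required. For example, 5% against 15% with success at 7 or more of 61 has alpha 3.2% and power 82.8%, but it only moves the bar. Power is 41% at a true 10%, the rule would declare success 31% of the time at a true 9%, and the article gives no source for 5%. Keeping 9% against 15% at 5% alpha and 80% power would need about 177 patients. A continuous residual-burden endpoint is likewise optional.
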